## Abstract

**Background:**

Radiotherapy (RT) is the standard of care for most advanced head and neck squamous cell carcinoma (HNSCC) and results in an unfavorable 5-year overall survival of 40%. Despite strong biological rationale, combining RT with immune checkpoint inhibitors does not result in a survival benefit. Our hypothesis is that the combination of these individually effective treatments fails because of radiation-induced immunosuppression and lymphodepletion. By integrating modern radiobiology and innovative radiotherapy concepts, the patient’s immune system could be maximally retained by (1) increasing the dose per fraction so that the total dose and number of fractions can be reduced (HYpofractionation), (2) redistributing the radiation dose towards a higher peak dose within the tumor center and a lowered elective lymphatic field dose (Dose-redistribution), and (3) using RAdiotherapy with protons instead of photons (HYDRA).

**Methods:**

The primary aim of this multicenter study is to determine the safety of HYDRA proton- and photon radiotherapy by conducting two parallel phase I trials. Both HYDRA arms are randomized with the standard of care for longitudinal immune profiling. There will be a specific focus on actionable immune targets and their temporal patterns that can be tested in future hypofractionated immunoradiotherapy trials. The HYDRA dose prescriptions (in 20 fractions) are 40 Gy elective dose and 55 Gy simultaneous integrated boost on the clinical target volume with a 59 Gy focal boost on the tumor center. A total of 100 patients (25 per treatment group) will be recruited, and the final analysis will be performed one year after the last patient has been included.

**Discussion:**

In the context of HNSCC, hypofractionation has historically only been reserved for small tumors out of fear for late normal tissue toxicity. To date, hypofractionated radiotherapy may also be safe for larger tumors, as both the radiation dose and volume can be reduced by the combination of advanced imaging for better target definition, novel accelerated repopulation models and high-precision radiation treatment planning and dose delivery. HYDRA’s expected immune-sparing effect may lead to improved outcomes by allowing for future effective combination treatment with immunotherapy.

**Trial registration:**

The trial is registered at ClinicalTrials.gov; NCT05364411 (registered on May 6th, 2022).

## Background

Definitive radiotherapy with or without concurrent chemotherapy is standard of care (SOC) for most locally advanced head and neck squamous cell carcinoma (HNSCC). As the five-year overall survival is only 40% [1], there is an urgent need for additional solutions to improve clinical outcomes. PD-(L)1 immune checkpoint inhibitors provide an attractive combinatorial treatment for increasing survival in metastatic HNSCC with potential synergetic effects with radiotherapy as a radiosensitizer [2–4], However, unfortunately, it was recently reported that the combination of anti-PD-L1 avelumab with chemoradiotherapy did not result in a survival benefit [5].

Our hypothesis is that the combination of these individually effective treatments failed because of both radiation-induced immunosuppression and lymphodepletion. While subablative doses of radiotherapy are believed to be highly immunogenic [6], there are valid concerns regarding the immunosuppressive effect of fractionated, wide (elective) field radiotherapy [7–9]. First, adequate naive T cell priming by dendritic cell (DC) mediated MHC-I cross-presentation may be abrogated in defective draining lymph nodes after elective nodal irradiation (ENI) [10], resulting in a reduced number of intratumoral antigen specific CD8^+^ effector T cells [11]. Second, large radiation fields are extremely toxic for circulating lymphocytes, which are very sensitive to radiotherapy [12]. Therefore, we believe that the key lies in reforming conventional fractionated radiotherapy, which typically consists of large radiation fields in 35 fractions.

For the improvement of clinical outcome in HNSCC through immunotherapy and radiotherapy combinations, HYpofractionated Dose-redistributed RAdiotherapy (HYDRA) offers a promising strategy. First, the elective lymphatic field dose can be reduced by the combination of advanced multimodality imaging [13]. Second, radiation volumes can be reduced without impairment of local control by state-of-the-art image-guided radiotherapy and dose delivery [14]. With these radiotherapy advancements, it has also become technologically feasible to redistribute the radiation dose towards a lower dose on the outside of the target volume, while increasing the dose per fraction inside the tumor [15]. Therefore, the total number of fractions can be reduced (hypofractionation) which may result in less lymphocyte damage. Furthermore, by using protons instead of photon radiotherapy the integral radiation dose can be lowered, additionally resulting in immune cell damage reduction [16]. Apart from the possible immune-sparing effect of HYDRA, recent insights in modern radiobiology suggest that hypofractionated radiotherapy may result in higher tumor control with less radiation-induced toxicity, by more efficiently targeting accelerated repopulation [17, 18], and/or because the alpha/beta of HNSCC may be lower than previously assumed [19].

The objectives of this study are to determine the safety of HYDRA given by proton or photon radiotherapy by conducting two parallel phase-I trials. HYDRA’s efficacy will be compared to the standard of care. The immune effects of HYDRA-protons will be evaluated by longitudinal immune profiling and compared to those of HYDRA-photons and SOC (with protons and photons). There will be a specific focus on actionable immune targets and their temporal patterns that can be tested in future hypofractionated immune-radiotherapy trials.

## Methods

A general overview of the treatment and study groups 1 to 4 is shown in Fig. 1, and described in more detail in the “design” section.

### Primary aim

To assess safety in terms of late grade 3–4 toxicity one year after the last patient has completed HYDRA for 25 HNSCC patients treated with HYDRA with proton therapy at HollandPTC (group 1) and in 25 HNSCC patients treated with HYDRA photon radiotherapy at the Erasmus MC (group 3). Patients will subsequently receive follow-up according to the standard of care up to five years after treatment for the evaluation of very late-onset toxicity. HYDRA is randomized with SOC radiotherapy for translational research purposes; a direct comparison of toxicity will statistically not be conclusive and is outside the scope of this study.

### Secondary aims

To evaluate the objective response rate three months after HYDRA (groups 1 and 3), defined by radiological response on CT or MRI (in combination with an FDG-PET scan for node positive disease) and/or histopathological confirmation of residual disease, in comparison to groups 2 and 4, respectively.To determine the efficacy of HYDRA (groups 1 and 3) in terms of in-field and nodal elective field tumor control, 1 year after the last patient is included, in comparison to group 2 and 4, respectively.To correlate the numbers of immune cell populations and the frequency of T cell subsets according to markers of maturation, activation, cosignaling, and chemoattractant receptors at baseline, with patient- and tumor parameters (tumor localization, TNM status, tumor subtype, comorbidities etc.) in groups 1–4.To monitor temporal changes in immune markers obtained in blood during/after treatment at six timepoints as specified in Fig. 1, and differences in these changes between groups 1–4.

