### Design

The safety of HYDRA will be evaluated in two parallel, noncomparative open label phase-I trials of patients treated with HYDRA-proton therapy (group 1) at HollandPTC and HYDRA-photon therapy (group 3) at Erasmus MC, The Netherlands. Patients will be selected for proton therapy according to standard of care Dutch model-based criteria. In brief, the protocol consists of a comparison of the photon plan and proton plan for the most favorable values of normal tissue complication probabilities (NTCPs) for dysphagia and xerostomia (grade ≥ II) [20].

For translational research purposes, each of the two parallel phase I trial cohorts will be compared with a study group receiving the standard of care treatment. To that end, HYDRA-proton therapy (group 1, *n* = 25) will be randomized by minimization in a 1:1 ratio with conventional fractionated proton therapy (group 2, *n* = 25), and HYDRA-photon radiotherapy (group 3, *n* = 25) will be randomized with conventional fractionated photon radiotherapy (group 4, *n* = 25). Randomization will be computer-generated, and minimization factors for randomization are: HPV status (positive vs. negative), tumor stage (I–II vs. III–IV) and the use of a concurrent radiosensitizer (yes vs. no). The PD-L1 Combined Positive Score (CPS) will be retrospectively determined and cannot be used for stratification, as the assessment typically takes multiple weeks and is not part of the initial work up.

We will determine efficacy to gain insight into whether HYDRA holds potential as a clinically effective hypofractionation protocol that should be tested in a subsequent trial. To increase statistical power, and because proton therapy is considered iso-effective to photon therapy, the efficacy of HYDRA will be determined for groups 1 and 3 combined and compared to the efficacy of conventional fractionated radiotherapy (groups 2 and 4). HYDRA should at least be iso-effective to conventional fractionated radiotherapy.

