### Interventions

#### HYDRA

The HYDRA dose prescriptions are delivered in 20 fractions. Gross tumor volume (GTV) is determined by the combination of PET-CT/MRI and ultrasound. The prescriptions consist of a focal inhomogeneous boost to the GTV of both the primary tumor and the pathological lymph nodes (CTV_5900 = GTV − 3 mm), a “conventional” simultaneous integrated boost (SIB) on the clinical target volume (CTV) of 55 Gy (CTV_5500 = GTV + 5 mm) and elective field radiotherapy of 40 Gy (CTV_4000 = GTV + 10 mm + elective lymph nodes). Delineations are in accordance with Grégoire et al. [21] and Biau et al. [22]. For the 55Gy and 40Gy CTVs, a 3 mm setup and 3%-range robustness is applied in case the patient is treated with proton therapy or a planning target volume (PTV) expansion margin of 3 mm is applied for photon radiotherapy. Target coverage is evaluated according to standard of care (D98 > 94% in voxel-wise minimum plan for protons, and D98 > 95% of the PTVs for photons [23]).

The focal boost to the GTV is delivered with a mean dose of 59 Gy and a maximum dose of 63.13 Gy (107% of 59 Gy). No more than 2% of the GTV should receive more than 63.13 Gy. The mean dose of 59 Gy corresponds to an equal late normal tissue toxicity probability after conventionally fractionated radiotherapy of 70 Gy in 35 fractions, considering an α/β = 3 for normal tissue. A 3 mm contraction margin is created to ensure that the 59 Gy boost always lies within the GTV (analogous to a negative PTV). If, after this step, there is no GTV_5900 volume left in the case of small tumor bulk, only a CTV_5500 boost will be prescribed. The mean dose of 59 Gy is a soft constraint: it is preferable but not obligatory and may be lower, depending on the 55 Gy boost dose constraints to the CTV.

The boost on the CTV has a mean dose of 55 Gy with an inhomogeneous distribution between 52.5 Gy at the border (95% of 55 Gy) and a maximum dose of 63.13 Gy within the GTV (107% of 59 Gy). No more than 2% of the CTV_5500 minus the GTV_5900 should receive more than 58.85 Gy (107% of 55 Gy). The volume that receives > 58.85 Gy should ideally be within the GTV_5900, but it is mandatory that this does not lie outside the CTV_5500. Discontinuation and treatment modification strategies are in accordance with the standard of care.

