Third, both intensity-modulated and image-guided radiotherapy (IMRT and IGRT, respectively) have been the standard of care for almost twenty years now, and have led to significant irradiation volume reduction without compromising clinical outcome [14]. Analysis of IMRT treatment reveals that recurrences are predominantly within the high dose target areas [34]. Optimizing local control without increasing toxicity can thus be achieved by redistributing the radiation dose, creating an inhomogeneous dose distribution towards the most (FDG-avid) active part of the tumor, instead of a conventional homogenous dose distribution with a 1 cm margin around the tumor area. This concept has formed the basis for the ARTFORCE trial, for which data are to be expected within the coming year [15]. As the dose directly outside the tumor is not increased, tumor control may be improved without additional toxicity. This concept of dose redistribution has already been proven in a randomized phase-III trial for prostate cancer [35].

A group from Brazil performed a phase-I trial of 20 × 2.75 Gy hypofractionated radiotherapy with concurrent cisplatin in advanced stage (75% stage IV) HNSCC and found that the acute toxicity rate was comparable to that of standard radiotherapy with concomitant chemotherapy [26]. Another prospective trial by the Mehanna group also showed that 25 × 2.6 Gy with concurrent chemotherapy resulted in tolerable acute toxicity in locally advanced oropharyngeal carcinoma [24]. From this, we may conclude that hypofractionation for HNSCC is well tolerated, at least in the acute phase and in large volume tumors, with and without the use of a concurrent radiosensitizer. Recently, a subgroup analysis of the PET NECK study was reported to support the use of a hypofractionated regimen during the COVID pandemic [25]. In this trial, 564 patients with locally advanced HNSCC receiving chemoradiotherapy were randomized to a planned neck dissection or active surveillance by FDG-PET. Three radiotherapy fractionation schedules (7, 6 or 4 weeks) were permitted: 56 patients received 20 × 2.75 Gy. There were no significant differences between the three fractionation schemes in terms of locoregional control, overall survival and quality of life after a minimum follow-up of two years.

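### The longer-term efficacy measure counts control only in treatment-defined compartments, so marginal recurrences could be counted differently between HYDRA and standard of care

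*Protocol article*

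**What the plan says.** Two of the secondary aims concern efficacy. One is objective response at three months, judged on imaging and/or histology without reference to any treated volume. The other covers the longer term and measures efficacy "in terms of in-field and nodal elective field tumor control, 1 year after the last patient is included, in comparison to group 2 and 4," respectively. There, group 1 is set against group 2 and group 3 against group 4. The Design section instead pools groups 1 and 3 against groups 2 and 4. It uses the result to gauge whether HYDRA merits a further trial, and adds: "HYDRA should at least be iso-effective to conventional fractionated radiotherapy". No margin or test is attached to that statement.

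On volumes, the HYDRA subsection of Interventions gives "CTV_5500 = GTV + 5 mm" for the 55 Gy boost and "CTV_4000 = GTV + 10 mm + elective lymph nodes" for the 40 Gy elective dose. The Standard of care (SOC) subsection gives doses (70 Gy boost and 54.25 Gy elective, in 35 fractions) but no margin. The only figure for a conventional margin is in the Discussion, where dose redistribution is proposed "instead of a conventional homogenous dose distribution with a 1 cm margin around the tumor area".

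The article does not say whether in-field refers to the boost volume or to all irradiated tissue. No stated aim uses local or regional control irrespective of field. Progression-free and overall survival are in the abbreviation list but in no aim.

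**The concern.** An efficacy endpoint should mean the same thing in both arms. Here the two counted compartments are drawn from each patient's own treatment plan, and the plan is what the trial varies. HYDRA lowers the dose towards the edge of the target, so recurrence at or near that edge is a failure it could plausibly add. Around a primary tumor, that is also where a measure restricted to in-field and nodal elective-field control is least sure to register an event.

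What is at stake is the judgement in the Design section on whether HYDRA is at least as effective as conventional fractionation and should go forward. With no margin or formal test stated, that judgement is likely to lean on point estimates of control, which a few unclassified failures can move.

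**Working it through.** The plan states no event rate, margin or power for efficacy. Its only sample-size figure is 4 × 25 = 100 patients, chosen pragmatically, so there is no efficacy calculation to reproduce.

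**1. Where a recurrence is counted.** The table uses the HYDRA volumes as stated, and two assumptions for the SOC boost margin.

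| Site of recurrence | HYDRA, in-field = boost volume | SOC, same reading | Both arms, in-field = any irradiated volume |
|---|---|---|---|
| Within 5 mm of the primary GTV | in-field | in-field | counted |
| 5–10 mm from the primary GTV | neither: outside CTV_5500, in the non-nodal part of CTV_4000 | in-field if margin is 1 cm; neither if 5 mm | counted (in SOC, if its treated volume reaches that far) |
| Elective nodal region | nodal elective | nodal elective | counted |
| Beyond all targets | neither | neither | neither |

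The arms differ by classification alone in only one row, under one reading and one assumed SOC margin. Photon plans add a 3 mm planning margin. If fields are judged on that margin, the affected band moves from 5–10 mm to 8–13 mm.

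**2. Size of the band.** Assume a spherical GTV of radius r mm and a 1 cm SOC margin. The HYDRA 55 Gy volume as a share of GTV + 10 mm is ((r + 5)/(r + 10))³:

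- r = 10: (15/20)³ = 42%
- r = 15: (20/25)³ = 51%
- r = 20: (25/30)³ = 58%
- r = 25: (30/35)³ = 63%
- r = 30: (35/40)³ = 67%

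The band is the remainder, 58% down to 33%. If SOC also uses GTV + 5 mm, the ratio is 1 and the boost-volume difference is zero.

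**3. Equal margins.** Suppose both arms used 5 mm and 10 mm. Under the boost reading, failures in the band would go uncounted in both arms, but the prescribed dose there would differ. With EQD2 = D(d + α/β)/(2 + α/β):

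- HYDRA, 40 Gy in 20 fractions (d = 2): 40 Gy at any α/β.
- SOC, 54.25 Gy in 35 fractions (d = 1.55): 54.25 × 11.55/12 = 52.2 Gy at α/β = 10 (assumed), and 54.25 × 4.55/5 = 49.4 Gy at α/β = 3.

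The number uncounted could therefore still differ by arm. The documents do not show that it would.

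**4. Effect on the comparison.** Let m_H and m_S be the failures uncounted in HYDRA and SOC, with n patients per arm. Treating control as a simple proportion, the difference (HYDRA minus SOC) shifts by (m_H − m_S)/n.

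| m_H − m_S | Pooled, n = 50 | Within a modality, n = 25 |
|---|---|---|
| 0 | 0 points | 0 points |
| 1 | 2 points | 4 points |
| 2 | 4 points | 8 points |
| 3 | 6 points | 12 points |

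**5. Scale.** Assume SOC control of 70%, 80% or 90%. With 50 per arm, a two-sided 5% comparison of proportions (normal approximation) has 18%, 21% or 29% power for a true deficit of 10 points. A 4 to 6 point shift would not by itself decide such a test, but it is not negligible beside differences of that order.

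**The case against.** The strongest reply is that no difference between arms is established. The SOC subsection states no margin, and the 1 cm figure is a general remark introducing a concept. The HYDRA boost is itself described as a conventional integrated boost drawn to cited guidelines. The Discussion adds that recurrences after modern planning lie mostly in high-dose areas, so marginal events may be few. A reader might infer from the stated volumes that HYDRA's boost is smaller than the SOC boost in this trial. The documents do not support that, and the difference may be zero.

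Second, in-field may mean any irradiated volume. A recurrence 8 mm from the primary GTV then lies within CTV_4000 and counts. Operational definitions may well be in the full protocol, and their absence from an article is not a fault. This stands as far as the definition goes. However, listing nodal elective control separately would be partly redundant under the wide reading. A definition alone would also not add a field-independent measure to the stated aims.

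Third, three-month objective response is independent of field, so it would be wrong to say that efficacy is counted only by field. It covers residual disease, not later recurrence.

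Fourth, extra nodal failures from the lower elective dose would occur in the nodal elective field and would be counted. A reader might think the endpoint hides them; it does not.

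Finally, efficacy is a secondary aim of trials described as noncomparative, and continuation and feasibility rest on toxicity. That limits the severity but leaves the stated efficacy comparison in place.

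**Conclusion.** The longer-term efficacy measure depends on treatment-defined compartments and is open to classification that differs by arm. Under the boost reading, a recurrence 5 to 10 mm from the primary GTV belongs to neither named compartment in HYDRA, and in SOC it is in-field only if the 1 cm margin applies. Under the wide reading, only recurrences beyond all targets are lost, and these are lost in both arms.

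A reader might conclude that the comparison is biased towards HYDRA. The documents show only that it can be. Bias needs more uncounted failures in HYDRA than in SOC, and nothing in the article gives those counts. Worked examples that drop failures from HYDRA alone would be invented. The supportable size is 2 points per excess uncounted failure in the pooled comparison and 4 points within a modality. The volume shares rest on a spherical GTV and the 1 cm SOC margin, and they vanish if SOC uses 5 mm.

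This is a cheap improvement of minor to moderate severity. No dose or margin is judged here.

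**What to change.** Restate the longer-term efficacy aim as locoregional control: any residual or recurrent tumor at the primary site or in the neck, whatever its relation to the treated volumes. This removes the dependence on arm-specific volumes under every reading of in-field.

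Keep in-field, marginal and elective location as a descriptive pattern-of-failure analysis. Classify each recurrence in both arms by its distance from the baseline GTV on the planning scan, with the same distance bands for HYDRA and SOC, rather than by each patient's own target volumes.

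The cost is a change of wording in the protocol or analysis plan and slightly more analysis work to map recurrences onto the baseline GTV. It relies on planning contours and follow-up imaging and needs no extra patients. The reported control rate may be somewhat less favourable. No dose, margin or treatment changes.

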### Design

The safety of HYDRA will be evaluated in two parallel, noncomparative open label phase-I trials of patients treated with HYDRA-proton therapy (group 1) at HollandPTC and HYDRA-photon therapy (group 3) at Erasmus MC, The Netherlands. Patients will be selected for proton therapy according to standard of care Dutch model-based criteria. In brief, the protocol consists of a comparison of the photon plan and proton plan for the most favorable values of normal tissue complication probabilities (NTCPs) for dysphagia and xerostomia (grade ≥ II) [20].

For translational research purposes, each of the two parallel phase I trial cohorts will be compared with a study group receiving the standard of care treatment. To that end, HYDRA-proton therapy (group 1, *n* = 25) will be randomized by minimization in a 1:1 ratio with conventional fractionated proton therapy (group 2, *n* = 25), and HYDRA-photon radiotherapy (group 3, *n* = 25) will be randomized with conventional fractionated photon radiotherapy (group 4, *n* = 25). Randomization will be computer-generated, and minimization factors for randomization are: HPV status (positive vs. negative), tumor stage (I–II vs. III–IV) and the use of a concurrent radiosensitizer (yes vs. no). The PD-L1 Combined Positive Score (CPS) will be retrospectively determined and cannot be used for stratification, as the assessment typically takes multiple weeks and is not part of the initial work up.

We will determine efficacy to gain insight into whether HYDRA holds potential as a clinically effective hypofractionation protocol that should be tested in a subsequent trial. To increase statistical power, and because proton therapy is considered iso-effective to photon therapy, the efficacy of HYDRA will be determined for groups 1 and 3 combined and compared to the efficacy of conventional fractionated radiotherapy (groups 2 and 4). HYDRA should at least be iso-effective to conventional fractionated radiotherapy.

